One such newer-generation progestin is norgestimate (NGM). NGM is a third-generation progestin derived from 19-nortestosterone [8]. It is rapidly hydrolyzed in vivo to norelgestromin, the primary active metabolite (75% to 80%), and levonorgestrel (20% to 25%) [9]. Both NGM and its metabolites have activity similar to endogenous progesterone but have a very poor affinity for androgen receptors and are therefore less androgenic than earlier progestins such as norgestrel, gestodene, or levonorgestrel [9,10]. In addition, unlike levonorgestrel, NGM increases levels of sex hormone–binding globulin in plasma, but does not bind to sex hormone–binding globulin, and is associated with reduced levels of free testosterone [11]. Data show that COCs containing NGM carry a lower risk of VTE than COCs containing cyproterone acetate, desogestrel, dienogest, drospirenone, or gestodene [12,13]. On the other hand, contraceptive patches containing norelgestromin are associated with a slightly higher incidence of VTE compared with levonorgestrel-containing COCs, presumably because of the high cumulative dose of EE that accompanies the transdermal route of administration [9].

Women want their contraceptives to be effective in preventing pregnancy, convenient, safe, and well tolerated, and with excellent cycle control [14]. Unscheduled bleeding has a number of negative impacts on a woman’s life, in addition to the inconvenience, including the potential for a negative effect on their sexual life and confusion about the status of their cycle [14]. Some women may interpret unscheduled bleeding as an indication that the COC is not working or interrupt use because of it [14]. Monophasic COCs containing 0.030-0.035 mg of EE offer women the greatest likelihood of a regular bleeding pattern with a low risk of estrogen-associated risks as well as the option of fewer periods by reducing or eliminating the placebo period altogether [15]. As well as preventing pregnancy and potentially providing better cycle control (increased regularity and reduced intermenstrual bleeding), COCs may also offer improvements in acne and premenstrual or menstrual symptoms, such as mood changes, headaches, and pelvic pain [16]. However, effects on these parameters vary between COCs [16].

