### End Points

The primary objective of the study is to investigate menstrual cycle control by evaluating breakthrough bleeding (ie, bleeding or spotting between the cyclically regular onset of menses) during the use of the monophasic NGM/EE 0.25/0.035 mg COC. This is measured by calculating the intermenstrual bleeding or spotting occurrence rate at the sixth cycle and comparing this with the rate at baseline.

Secondary outcomes include the change from baseline at visits 2 and 3 in other parameters of cycle control (frequency, duration, regularity, participant-determined flow volume, and unscheduled bleeding), GAGS score, POMS, FSFI, and dysmenorrhea severity based on the VAS rating. Adherence and contraceptive failure rate over the 6-month study period are also secondary outcomes, as are changes from baseline in the metabolic, hormonal, or coagulation parameters in the subgroup of participants from Genoa. Adherence is being evaluated as a percentage of tablets taken, based on the medication returned by participants at each visit. Contraception failure is defined as the proportion of women who become pregnant during the 6-month study period. The reasons for any contraception failure will be identified and listed (eg, discontinuation or poor adherence).

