### Statistical Analysis

Based on the previous large-scale study with NGM/EE 0.25/0.035 mg, the rate of breakthrough bleeding is expected to decrease from 4.5% before use to 3% after 6 cycles, and the rate of intermenstrual spotting to decrease from 9% to 4% [17]. Therefore, a sample size of 175 participants would have 80% power to detect a treatment effect on breakthrough bleeding at a 1-sided α level of 5%. To account for a potential dropout rate of 30%, we plan to screen 240 women for eligibility and enroll 228 participants, an average of 38 participants at each of the 6 centers.

Two datasets have been defined for analysis: the per-protocol set, which includes all participants with full treatment adherence and no major protocol deviations, and the intention-to-treat set, which includes all enrolled participants who received at least 1 dose of NGM/EE 0.25/0.035 mg. The primary outcome will be evaluated only in the per-protocol population to avoid any effects of noncompliance on the interpretation of this outcome. However, secondary efficacy outcomes and safety will be assessed in the intention-to-treat population using robust statistical methods against missing data, like linear mixed models.

Continuous variables will be described using the mean and standard deviation if they are normally distributed or using the median and interquartile range if nonnormally distributed. The distribution of these variables will be assessed using the 2-tailed Student *t* test for paired data or the Wilcoxon signed rank test. Categorical variables will be described using frequencies and percentages and compared using the chi-square test or Fisher exact test [25]. There will be no imputation for missing data, and data from unscheduled visits will not be included in the analysis. No adjustment for multiplicity will be made to adjust for a type I error in secondary end points. A *P* value of .05 is considered to be statistically significant.

All statistical analyses will be performed using the R statistical software (version 3.5 or later; R Foundation for Statistical Computing). The final analysis will be completed after all participants have completed the study, any queries have been resolved, and the database has been locked.

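### The primary outcome is analysed only in fully adherent women, a selection linked to bleeding that probably flatters the cycle-6 rate by an amount the protocol cannot quantify

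*Protocol article*

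**What the plan says.** All references are to the protocol article.

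- **Primary outcome (End Points).** The occurrence rate of intermenstrual bleeding or spotting at the sixth cycle is compared with the rate at baseline. There is no control group.
- **Primary analysis set (Statistical Analysis).** "The primary outcome will be evaluated only in the per-protocol population to avoid any effects of noncompliance on the interpretation of this outcome". That set "includes all participants with full treatment adherence and no major protocol deviations".
- **The other set (Statistical Analysis).** The protocol also defines "the intention-to-treat set, which includes all enrolled participants who received at least 1 dose of NGM/EE 0.25/0.035 mg", but uses it elsewhere: "secondary efficacy outcomes and safety will be assessed in the intention-to-treat population", with methods described as robust to missing data.
- **Missing data (Statistical Analysis).** "There will be no imputation for missing data".
- **How adherence is measured (End Points).** "Adherence is being evaluated as a percentage of tablets taken, based on the medication returned by participants at each visit". It is therefore known only after treatment has begun.
- **Link between bleeding and continued use (Introduction).** "Some women may interpret unscheduled bleeding as an indication that the COC is not working or interrupt use because of it".
- **Acknowledged limitations (Strengths and Limitations).** The absence of a control group and the short follow-up are named. Selection into the analysis set is not.

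**The concern.** By the protocol's own account, a woman who bleeds between periods may stop or interrupt the product. If she does, she is no longer fully adherent and leaves the only set in which the primary outcome is evaluated. Membership of that set can thus be a consequence of the outcome. The women who remain are then compared with baseline, and the difference is read as the product's effect on cycle control.

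A single-arm study has no comparator in which similar selection might partly cancel. The expected direction favours the result that the Discussion anticipates. The stated aim is cycle control during use of the product, which concerns women who start it, not only those who complete six cycles with full adherence. The plan is also uneven: the secondary outcomes get the all-treated set and methods that tolerate missing data, while the outcome that carries the conclusion gets neither.

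**Working it through.** **1. The plan's own effect sizes (Statistical Analysis).** Breakthrough bleeding: 4.5% − 3% = 1.5 points. Intermenstrual spotting: 9% − 4% = 5 points. The documents give neither the share of women who will fall outside the per-protocol set nor their bleeding rate, so everything below is illustration.

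**2. What selection alone could produce.** Let *r* be the cycle-6 rate in all treated women, *e* the excluded share, *k* the ratio of the cycle-6 rate in excluded to retained women, and *p* the per-protocol rate. Then

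*r* = (1 − *e*)·*p* + *e*·*k*·*p*, so *p* = *r* / [(1 − *e*) + *e*·*k*].

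Assume no true change and the same 4.5% baseline in both groups, so *r* = 4.5%. The values of *e* and *k* are assumptions. The protocol's 30% is a dropout allowance, used here only as a reference point for *e*.

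| *e* | *k* | denominator | per-protocol rate | spurious drop (points) |
|---|---|---|---|---|
| any | 1 | 1.000 | 4.50% | 0.0 |
| 15% | 1.5 | 1.075 | 4.19% | 0.3 |
| 15% | 2 | 1.150 | 3.91% | 0.6 |
| 15% | 3 | 1.300 | 3.46% | 1.0 |
| 30% | 1.5 | 1.150 | 3.91% | 0.6 |
| 30% | 2 | 1.300 | 3.46% | 1.0 |
| 30% | 3 | 1.600 | 2.81% | 1.7 |

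Only the last row reaches the planned 1.5 points.

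The End Points section counts bleeding *or* spotting. If no woman has both (a further assumption), the baseline is 4.5% + 9% = 13.5% and the expected cycle-6 rate is 3% + 4% = 7%, a planned fall of 6.5 points. With 30% excluded, the per-protocol rate under no true change is 13.5/1.15 = 11.7%, 13.5/1.30 = 10.4% or 13.5/1.60 = 8.4%. The spurious drops are 1.8, 3.1 and 5.1 points. These are material, but below the planned 6.5 in every case.

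**3. The role of baseline.** The outcome is a change, and the per-protocol baseline comes from the same women. Let *f*P and *f*E be the falls in retained and excluded women. The fall in all starters is (1 − *e*)·*f*P + *e*·*f*E, so

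bias in the change = *f*P − fall in all starters = *e*·(*f*P − *f*E).

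The bias depends on the difference in falls, not in cycle-6 rates. Example on the spotting scale: retained women go from 9% to 4%, and excluded women (30%) from 13% to 8%. All starters go from 0.7 × 9 + 0.3 × 13 = 10.2% to 0.7 × 4 + 0.3 × 8 = 5.2%. The fall is 5.0 points, the same as per protocol, so the bias is zero even though the excluded women bleed twice as often at cycle 6.

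**The case against.** A per-protocol analysis answers a legitimate question, cycle control under full adherence, and the protocol gives that rationale openly. This stands: the analysis is worth keeping, and the fault lies in its being the only one.

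The Introduction says only that some women may interrupt use, and the size of any bias is unknown. This also stands, and it is why the direction is called probable here. As step 3 shows, the bias in the change can vanish.

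Unscheduled bleeding is a secondary outcome and will be analysed in all treated women. This mitigates only in part. Table 1 marks that item as not applicable to women not taking gonadal steroids, and hormonal contraceptive use in the month before entry is an exclusion criterion. A baseline comparison for it is therefore unclear, and it does not replace the primary before-after comparison.

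Three stronger readings are tempting but not supported:

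- *That the reported fall is overstated by a third or more.* Taking the spotting rates alone, with 30% excluded at 8–12% in cycle 6, all starters would be at 0.7 × 4 + 0.3 × 8 = 5.2% to 0.7 × 4 + 0.3 × 12 = 6.4%. The 5.0-point fall is then overstated by 5.0/3.8 − 1 = 32% to 5.0/2.6 − 1 = 92%. Other equally admissible inputs give far less. With 10% excluded at 6–8% it is 5.0/4.8 − 1 = 4% to 5.0/4.6 − 1 = 9%; with 20% excluded, 5.0/4.6 − 1 = 9% to 5.0/4.2 − 1 = 19%. All of these assume equal baselines.
- *That one missed tablet excludes a woman.* Adherence is measured as a percentage, and a numeric cut-off is a detail that an article may leave to the full protocol.
- *That this restriction is what undermines power.* For 9% to 4%, a one-sided McNemar approximation with correlation 0 to 0.4 gives only 56–74% at 160 women (228 × 0.7), before any adherence exclusion. That is largely a separate sample-size matter.

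**Conclusion.** The point holds on the text. The restriction to the per-protocol set is an affirmative choice, not a detail deferred to a plan that is not shown. It makes the sole primary analysis condition on a post-baseline variable that the protocol itself ties to bleeding. The likely direction is a lower cycle-6 rate than among all women who start the product.

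The size is not identifiable. The range of 0.6 to 1.7 points for breakthrough bleeding rests on three assumptions: no true change, 30% excluded and equal baseline rates, with excluded women bleeding 1.5 to 3 times as often. With 15% excluded it is 0.3 to 1.0 points, and with equal bleeding rates it is zero. What can be said firmly is that the plan contains no analysis of the primary outcome that would show whether the selection matters.

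**What to change.** 1. Delete the restriction to the per-protocol set. Make the existing at-least-one-dose set the primary analysis set for the primary outcome or, at minimum, report it beside the per-protocol result with equal prominence.
2. Estimate the cycle-6 versus baseline contrast from the paired baseline and diary-cycle data, so that women who leave early contribute the cycles they recorded. The method must remain valid when dropout depends on earlier bleeding: a likelihood-based mixed logistic model or weighted GEE. Unweighted GEE is not generally valid in that case. Neither needs imputation, so the missing-data statement can stand.
3. Keep the model simple. At 4% of about 160 women, only about 6 events are expected at cycle 6 (0.04 × 160 = 6.4).
4. State how women who stop before cycle 6 are handled, and add one sensitivity analysis that counts discontinuation for bleeding as bleeding at cycle 6. The Procedures section already has the investigator record reasons for early withdrawal.
5. Keep the per-protocol analysis, labelled as a supportive estimate under full adherence.

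The cost is a change of wording and slightly more analysis work before database lock. No new data are needed, because diaries and withdrawal reasons are already collected. The downside for the sponsor is a probably less favourable cycle-6 rate.

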Finally, our study includes an assessment of the severity of pain associated with menstruation in accordance with international consensus recommendations [19]. Previous studies have evaluated the incidence of pain in women taking monophasic NGM/EE but not the severity of pain [17,18]. This is an important distinction because pain is a continuum rather than a binary outcome. Data indicate that at least 90% of women experience some kind of discomfort during menstruation [34], although their experiences vary across time [35]. Dysmenorrhea is often underreported for many reasons, including that symptoms are considered normal or that women find the symptoms tolerable [36]. Therefore, pain was likely underreported in clinical trials because participants may only report pain that is new, worse, or acute [34]. Using a tool like VAS will provide nuanced information about both the incidence and severity of menstrual pain in women taking NGM/EE 0.25/0.035 mg. Limitations of our study are the absence of a control group and the relatively short duration of follow-up.

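### The binary primary endpoint compares the same women before and on treatment, but the only categorical tests named, chi-square and Fisher, assume independent samples

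*Protocol article*

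**What the plan says.** The End Points section of the protocol article defines the primary measure as "calculating the intermenstrual bleeding or spotting occurrence rate at the sixth cycle and comparing this with the rate at baseline". There is no comparator; under Strengths and Limitations the authors write: "Limitations of our study are the absence of a control group and the relatively short duration of follow-up". The primary outcome is analysed in the per-protocol set only.

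The Statistical Analysis section then assigns tests by type of variable. For continuous variables pairing is written in: a t "test for paired data or the Wilcoxon signed rank test". For categorical variables it is not: "Categorical variables will be described using frequencies and percentages and compared using the chi-square test or Fisher exact test". No McNemar test, conditional logistic model, GEE or other paired binary method appears in the article. A separate sentence has secondary efficacy outcomes and safety assessed "using robust statistical methods against missing data, like linear mixed models"; it does not cover the primary outcome.

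**The concern.** Each woman contributes two yes/no observations, one at baseline and one at cycle 6. Chi-square and Fisher, applied to the two rates, treat these as 350 observations from two unrelated groups of 175. If a woman who bled or spotted at baseline is more likely to do so at cycle 6, the two rates are positively correlated, and the unpaired test overstates the variance of their difference. Its P value is then too large on average, and a real reduction is more easily missed. This affects the one endpoint on which the study is sized.

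**Working it through.** **Inputs.** From Statistical Analysis: 175 evaluable women, 80% power, one-sided 5%; breakthrough bleeding 4.5% to 3%; intermenstrual spotting 9% to 4%. The within-woman correlation (phi) is not given; I assume 0 to 0.5.

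**The plan's own figure.** The 175 does not reproduce from 4.5% to 3%. The one-sided two-sample formula gives

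n = [1.645·√(2·0.0375·0.9625) + 0.842·√(0.045·0.955 + 0.03·0.97)]² / 0.015² ≈ 1983 per period,

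and power at 175 is 18%. So 175 does not reveal which test was intended. This is a separate issue, used below only to show what changing the test can and cannot do.

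**Paired model.** With rates p0 and p1:
- p11 = p0·p1 + phi·√[p0(1−p0)p1(1−p1)]
- p10 = p0 − p11 (bleeds at baseline only)
- p01 = p1 − p11 (bleeds at cycle 6 only)

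Example, 9% to 4% at phi 0.3: p11 = 0.0036 + 0.3 × 0.0561 = 0.0204, p10 = 0.0696, p01 = 0.0196. Expected discordant pairs: 175 × 0.0892 = 15.6.

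**Level when nothing changes.** With equal rates the true variance of the difference is (1 − phi) times what the unpaired test assumes. Its real one-sided level is therefore about 1 − Φ(1.645/√(1 − phi)): 2.5% at phi 0.3 (1.645/0.837 = 1.97) and 1.0% at phi 0.5 (1.645/0.707 = 2.33). Simulation of 175 pairs (200,000 runs per setting), 9% at both times, agrees:

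| phi | Chi-square | Fisher | McNemar (asymptotic) |
|---|---|---|---|
| 0 | 5.2% | 3.4% | 5.0% |
| 0.1 | 4.3% | 2.7% | 5.0% |
| 0.2 | 3.4% | 2.0% | 4.8% |
| 0.3 | 2.5% | 1.4% | 4.9% |
| 0.5 | 1.1% | 0.5% | 5.1% |

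**One-sided power, 9% to 4%, n = 175 (simulated).**

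| phi | Chi-square | Fisher | McNemar (asymptotic) | McNemar (exact) |
|---|---|---|---|---|
| 0 | 61% | 52% | 60% | 53% |
| 0.1 | 62% | 53% | 65% | 57% |
| 0.2 | 63% | 52% | 69% | 61% |
| 0.3 | 63% | 53% | 74% | 66% |
| 0.5 | 65% | 53% | 88% | 79% |

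**One-sided power, 4.5% to 3%, n = 175 (simulated).**

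| phi | Chi-square | McNemar (asymptotic) | McNemar (exact) |
|---|---|---|---|
| 0 | 18% | 18% | 12% |
| 0.3 | 14% | 22% | 12% |
| 0.5 | 10% | 26% | 13% |

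The most favourable case for McNemar is that no woman newly bleeds (p01 = 0, discordant proportion 0.015). The normal approximation then gives Φ[(0.015·√175 − 1.645·√0.015)/√(0.015 − 0.015²)] = Φ(−0.025) = 49%.

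**The case against.** **What stands.** The size of the loss rests on a correlation that the article does not give. At zero correlation the chi-square and asymptotic McNemar tests are practically equal. The gain also depends on the version of McNemar: with few discordant pairs the exact test is itself conservative, and at phi 0.2 (61%) it does no better than the unpaired chi-square (63%). Under positive correlation the named test errs on the safe side.

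**What does not stand.** One could say that chi-square is loose wording for McNemar, or that an analysis plan will settle it. But chi-square is coupled with Fisher's test, which has no paired form, and pairing is spelled out for continuous variables just before. This is a test named wrongly, not a detail left out. The mixed-model sentence does not help either: it covers secondary efficacy outcomes and safety, and it names a model for continuous outcomes.

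**Stronger readings that the article does not support.**
- A reader might infer a raised risk of a false positive. With positive correlation the reverse holds; only a negative correlation makes the chi-square test slightly liberal (5.3% to 5.5% at phi −0.03).
- A reader might imagine chi-square run on the baseline-by-cycle-6 table, where it tests association, not change. With 9% at both times it would reject in about 66% of studies at phi 0.2 and 98% at phi 0.4. But End Points speaks of comparing rates, and nothing prescribes that use.
- A reader might conclude that every categorical comparison is affected. Pregnancy and adverse events are not before-after comparisons, and secondary efficacy outcomes may be handled by repeated-measures methods. The point is firm for the primary.
- A reader might say that the planned confidence interval is wrong. The article specifies none.
- The sentence "The distribution of these variables will be assessed using the 2-tailed Student" (continuing with the t test) is a wording slip, and paired tests beside mixed models are an ambiguity. Neither adds weight here.

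**Conclusion.** The point holds for the primary endpoint. The article states a test for independent samples for a paired binary comparison. Under an assumed correlation of 0 to 0.5 and 175 evaluable women, the chi-square test's real one-sided level runs from about 5% down to 1.1%. For 9% to 4%, the power given up against asymptotic McNemar runs from none to about 23 points (88% − 65%); against exact McNemar the difference runs from a gain of 8 points for the unpaired chi-square (61% − 53%) to a loss of 14 (79% − 65%).

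The harm is lost power under positive correlation, not false claims of benefit. It would also be wrong to expect the paired test to rescue the sample size: for 4.5% to 3% it gives at most 49%, against the stated 80%. The correction is still worth making, because the error sits on the primary endpoint and costs almost nothing to remove.

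**What to change.** In Statistical Analysis, limit the chi-square and Fisher tests to comparisons between independent groups, if any are planned. For the primary endpoint, and any other before-after binary endpoint, name:
- McNemar's test in asymptotic or mid-P form, or exact if discordant pairs are very few, with the version and the rule for choosing it fixed in advance; and
- a paired 95% confidence interval for the difference in proportions.

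A logistic GEE with the woman as cluster is an acceptable alternative. Report the full baseline-by-cycle-6 table, so that the discordant counts are visible.

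The cost is a wording change in the protocol and any analysis plan, made before database lock. It needs no new data, visits or participants. The sample size justification needs its own correction.

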## Results

Study enrollment began in July 2023 and is expected to be complete by December 2025. The last participant’s last visit is anticipated to be in June 2026, and data analysis will be complete by October 2026.

